### Data

All data are collected and stored confidentially in accordance with General Data Protection Regulation (GDPR). Data are stored in a separate approved and secure database (REDCap), which only the investigators and sponsor have access to, and only the investigators will enter data to reduce the risk of mistakes. Data are processed in Excel and the statistical software R and are stored in accordance with the Danish Capital Region’s requirements for research data. The GCP monitor will control the data entry by comparing REDCap information with the patient’s journal for 10% of the participants. The Danish GCP unit (https://gcp-enhed.dk/) is independent from the sponsor and competing interests and will audit the trial conduct with regular visits.

## Statistics

### Sample size calculation

Based on the study by Knight et al. [5], 6.5% in the antibiotic group had a subsequent superficial or deep infection after obstetric tear. The corresponding number for the placebo group was 12.8%. Similarly, they found a lower prevalence of wound dehiscence, 11% in the antibiotic treated group compared to 21% in the placebo group. Based on a Danish Cohort study, the risk of wound dehiscence in women with second degree perineal tears was 18% and the risk of wound infection 9% [3].

We assumed that the frequency of wound dehiscence and/or infection for second degree tear after vaginal delivery is approximately 20%. We further hypothesized that the risk of subsequent infection and/or dehiscence can be reduced by 50% by administering oral amoxicillin 500 mg/clavulanic acid 125 mg given as three doses in the first day after birth compared to placebo. With a dropout rate of 10%, 221 women must be included in each group, to find a significant difference between groups with a significance level of 0.05 and a power of 80%. The total number of women with second degree perineal tear to be included in this study is 442 with 1:1 randomization.

### Interim analysis

We plan to conduct an interim analysis when 50% of the planned participants are included. The interim analysis will be performed to ensure the expected frequency of wound dehiscence and/or infection in the over-all study population. The blinding of the study will be kept during the interim analysis. Since we expect a frequency of approximately 20% in the control group and approximately 10% in the antibiotic group, we would expect a frequency of 15% in the total trial population. If the interim analysis calculates a total frequency of approximately 15% or more, the study will be continued until the planned 442 women are included. If the interim analysis demonstrates a significantly lower total frequency than expected, we will calculate the additional number of women needed to be included to maintain the power in the study and extend the study period accordingly. The re-calculation will be based on the calculated frequency during the first half of the trial using the same expected effect of the intervention in reduction of wound dehiscence and/or infection.

### Outcome analysis

The unblinding of the data in the study takes place after the last participant has completed the 1-year control visit. The groups will be analyzed descriptively with median, range, and IQR (interquartile range) and quartiles 1 and 3 (Q1 and Q3). The results are calculated with proportion and percentage and with univariable and multivariable analyses. Our primary outcome is wound dehiscence and/or infection, which will be calculated using *χ*^2^ tests to compare the antibiotic group with the placebo group. Secondary outcomes related to long-term symptoms will be analyzed with *χ*^2^ test or Fisher’s exact test or with *t*-test or Mann–Whitney test depending on whether the data are normally distributed or not. All results will be analyzed based on intention-to-treat analysis. Missing data will be indicated for all variables and will basically be handled with case-wise deletion, where we leave the subject’s results omitted only for the analyses where data are missing. We will perform subanalyses focusing on wound dehiscence as clinically significant or insignificant as well as for wound dehiscence or infection that causes treatment or further follow-up visits. Statistical analyses are performed with the statistical software R (https://cran.r-project.org/).

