### Intervention

Placebo and amoxicillin 500 mg/clavulanic acid 125 mg will be obtained from The Capital Region Pharmacy, who will be responsible for the randomization process. The randomization will occur during the packing chronological ID-number medicine boxes each containing either placebo or the intervention medication. By establishing the randomization prior to enrollment, we avoid selection bias at the inclusion process. The medication will be stored in a locked medicine room at the maternity ward. The principial investigators will be responsible for control and handling of the trial medicine.

At inclusion, the women will be given the next chronological ID-number corresponding to a medicine box. The participant is then randomized to have either amoxicillin 500 mg/clavulanic acid 125 mg or placebo medicine for 1 day after delivery (three doses in total administrated with 8-h intervals). The blinding will be kept for both the participants, the including doctor, the principal investigators, and all four authors of this paper until the last visit for the last patient.

The randomization will be an individual level randomization with an allocation ratio of 1:1 to amoxicillin 500 mg/clavulanic acid 125 mg or placebo. Randomization will occur in blocks to reduce the risk of unblinding. The randomization process will not be stratified. The randomization will be based on a computer-generated random-number allocation sequence stored at the pharmacy. The randomization sequence will not be available to staff involved in data management, analysis, report writing, or patient care until breaking of the randomization code.

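### The primary chi-square test is valid, but it leaves unused an injury type known for every woman before allocation; adjusting for it is an optional, nearly free improvement

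*Protocol article*

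**What the plan says.** All references are to the protocol article.

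- **Outcome analysis** names the primary test: "Our primary outcome is wound dehiscence and/or infection, which will be calculated using *χ*^2^ tests to compare the antibiotic group with the placebo group". The same section mentions univariable and multivariable analyses in general terms, without covariates and without linking them to the primary outcome.
- **Intervention** describes 1:1 allocation in blocks and adds: "The randomization process will not be stratified".
- **Screening** admits women with a second-degree tear, an episiotomy, or both. Injury type is therefore established for every woman before she receives a numbered medicine box.
- **Initial consultation** says the time of the first visit is noted so that the final analysis can adjust for it. That is a post-randomisation variable. No section names injury type as a stratification factor, covariate or subgroup.
- **Sample size calculation** uses one event rate for all women: "We assumed that the frequency of wound dehiscence and/or infection for second degree tear after vaginal delivery is approximately 20" per cent, halved by treatment. It concludes: "With a dropout rate of 10%, 221 women must be included in each group".

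**The concern.** The trial pools two kinds of wound. If episiotomies and spontaneous tears differ in their risk of dehiscence or infection, injury type explains part of the outcome. An analysis that includes it is then slightly more powerful than one that does not. It also removes from the estimate any shift caused by a chance excess of one injury type in one arm. Without stratification, nothing in the allocation limits such an excess.

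The covariate costs nothing to obtain, because a woman cannot be enrolled without it. What is at stake is a modest gain in precision, and only if injury type is prognostic.

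**Working it through.** **1. Reproduce the plan's sample size.** Inputs from Sample size calculation and Interim analysis: 20% on placebo, 10% on antibiotic, significance level 0.05, power 80%, dropout 10%. Two-sided testing is assumed, because the article does not state sidedness and a one-sided test would give 175 per arm.

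n per arm = [1.96 × √(2 × 0.15 × 0.85) + 0.8416 × √(0.20 × 0.80 + 0.10 × 0.90)]² / 0.10² = [0.990 + 0.421]² / 0.01 ≈ 199.

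199 / (1 − 0.10) = 221.1, against 221 stated. With a continuity correction the result would be 244, so the plan's figure corresponds to the uncorrected, unadjusted chi-square test. At 199 evaluable per arm that test has 80.0% power by formula.

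**2. How large can chance imbalance be?** For an episiotomy share s, the standard deviation of the between-arm difference in share is √(2s(1 − s)/199). The article does not give s, so a range is used:

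- s = 10%: 1.96 × √(2 × 0.09/199) = 5.9 points
- s = 30%: 1.96 × √(2 × 0.21/199) = 9.0 points
- s = 50%: 1.96 × √(2 × 0.25/199) = 9.8 points

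An imbalance of about 6 to 10 points or more is therefore expected in roughly 1 trial in 20.

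**3. What does this do to the risk difference and to power?** The table is for s = 30%, with 199 evaluable per arm, an overall placebo risk of 20% and the risk halved in each injury group (40,000 simulated trials per row). The stratified test is Cochran-Mantel-Haenszel. The shift is the 95th-percentile imbalance times the placebo risk gap between injury types.

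| Odds ratio, episiotomy vs tear (assumed) | Placebo risk, tear / episiotomy | Power, chi-square | Power, stratified test | Shift in risk difference |
|---|---|---|---|---|
| 1 | 20.0% / 20.0% | 80.8% | 80.3% | 0 |
| 1.5 | 18.0% / 24.7% | 81.0% | 80.8% | 0.6 points |
| 2 | 16.5% / 28.3% | 80.7% | 80.9% | 1.1 points |
| 3 | 14.3% / 33.3% | 80.8% | 81.8% | 1.7 points |
| 4 | 12.8% / 36.9% | 81.1% | 82.6% | 2.2 points |

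Example, odds ratio 2: 0.090 × (0.283 − 0.165) ≈ 0.011.

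Over shares of 10% to 50%, the stratified test changes power by about −0.5 to +1.5 points. The shift is 0.8 to 1.1 points at odds ratio 2 and 1.7 to 2.2 points at odds ratio 4. These shifts use the placebo risk gap. If treatment halves the risk and the imbalance is split evenly between arms, they are (1 + 0.5)/2 = 0.75 times as large.

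**4. Logistic adjustment for injury type alone.** In a separate simulation, the gain over the chi-square test is about 0 points at odds ratios of 1 to 1.5, 0.7 at 2, 1.2 at 3 and 1.8 at 4. There is no loss beyond simulation error where injury type does not matter.

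**5. Type I error.** It is 0.050 to 0.053 for the unadjusted test across the settings and 0.053 for the adjusted analysis in a null run. Both are acceptable.

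**6. Scale.** The smallest observed difference that reaches significance is about 1.96 × √(2 × 0.15 × 0.85/199) = 7.0 points, and the planned difference is 10 points. A shift of 1 to 2 points would matter only for a borderline result.

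**The case against.** The strongest reply is that nothing here needs correcting. Randomisation is unstratified, so the analysis omits no stratification factor. The chi-square test is the one the trial was sized for, and it meets its target without covariates. Its confidence interval already allows for random imbalance. All of that stands.

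It also stands that the article never says injury type is prognostic. The Background gives one pooled figure for dehiscence after a tear or an episiotomy. Every odds ratio and episiotomy share above is therefore an assumption, and at odds ratios of 1.5 or below there is nothing to gain in power.

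Three stronger readings are tempting, and the article supports none of them:

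- A reader might infer that the plan gives up material power or is exposed to bias. The calculations show at most about 2 points of power, and then only if injury type is strongly prognostic.
- A reader might infer that the mention of multivariable analyses leaves the deciding result open to dispute after unblinding. The chi-square test is named for the primary outcome, so the deciding test is fixed. The covariates of further analyses are what an article may leave to the full protocol or analysis plan.
- A reader might want instrumental delivery in the model as well, for a larger gain. The article does not list mode of delivery among the data collected, so it cannot be called free.

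The objection leaves one point unanswered: a baseline covariate that is necessarily known for every woman goes unused, and using it does no harm.

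**Conclusion.** The planned primary test is not in error, and its 80% power and 221 per arm stand. Adjusting for injury type is an optional improvement of small and uncertain size: about 0 points of power at an odds ratio of 1 to 1.5, under 1 point at 2, and about 1 to 2 points at 3 to 4. It would also remove a 95th-percentile chance shift in the risk difference of about 1 point (odds ratio 2) to 2 points (odds ratio 4).

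These figures assume 199 evaluable women per arm, 20% versus 10% overall, and an episiotomy share of 10% to 50% for the imbalance and stratified-test results. The article gives neither that share nor the risk by injury type.

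**What to change.** Before unblinding, and only if the investigators wish to take up the gain:

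- Make the primary analysis a logistic model with arm and injury type, reported as a standardised (marginal) risk difference with 95% CI.
- Code injury type as any episiotomy versus second-degree tear only. The entry criterion allows both injuries in one woman, so a coding rule is needed.
- Keep the chi-square test as the supporting unadjusted result.
- Add mode of delivery only if the trial already records it.

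The cost is a change of analysis wording and a few lines of R. Injury type needs no new data, visits or participants, and the sample size does not change. Unblinding is planned only after the last 1-year visit, so the covariate can be fixed while the data are still blinded.

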### Publication

All results—regardless of the magnitude or direction of effect—will be published in peer-reviewed international papers and will be presented at national and international conferences. There are no publication restrictions for the trial. Authorships will be based on the criteria stated in the recommendations for publication from International Committee of Medical Journal Editors. All study participants will be offered information about the result of the study.

## Discussion

This randomized controlled double-blinded study evaluates whether oral antibiotics can prevent wound dehiscence or infection after second degree obstetric tears or episiotomy compared to placebo. The study has the possible advantage for the group receiving antibiotics that they might have a lower risk of infection and wound dehiscence compared to the control group. Conversely, this group also has a risk of side effects to the medication. The antibiotic used in this study is a frequently used medication that can also be used in breastfeeding women [7]. The placebo group will most likely not experience any side effects but conversely do not have the possible protective effect with respect to risk of infection or wound dehiscence. It is not standard in Denmark to treat second-degree tear or episiotomy with antibiotics and therefore the placebo group in this study is treated in accordance with national guidelines. Both groups are offered consultation with a physician in the first 2 weeks as well as 9–12 months after birth, which is not offered routinely today. This may be of concern to some of the women who will think more about the tear and recovery than they otherwise would have done. However, it can also have a calming effect on some of the trial participants that the tear and healing is being monitored and that it is assessed by a health care professional. For participants experiencing infection and/or wound dehiscence, the initial consultation can result in earlier diagnosis and treatment and, thus, potentially improved outcome. Conversely, some women might have tendency to postpone contact with their own general practitioner for a check-up, because they are waiting for the scheduled appointment in study. However, the participants are thoroughly informed about the importance of contacting a physician if they experience any discomfort before the initial consultation.

If our study finds a significant reduction in wound dehiscence and/or infection, introducing preventive oral antibiotic as a standard treatment for women with a second-degree tear or episiotomy, a frequent outcome in the vaginal delivery, needs to be considered thoroughly, especially since this population consist of breastfeeding women and due to the overall overconsumption of antibiotics worldwide. Antibiotics to breastfeeding women always have the potential to be transmitted to the baby with possible short- and long-term complications. In this study, the antibiotics are only administrated within the first 24 h of the delivery before the milk production has started. We therefore expect no clinically relevant doses transmitted to the baby. Notably, if the prophylactic antibiotics decreases the number of infections at the initial consultation, this study has the potential to reduce the amount of antibiotic prescribed at later timepoints where the risk of transmission to the baby is increased. With regard to the overall overconsumption of antibiotics, Knight et al. [5] found that the total use of antibiotics in the post-partum period was decreased for the participants who received prophylactic antibiotics compared to placebo. If this study support this finding, it has the potential to reduce the overall use of antibiotic in the postnatal period.

If this study finds that three doses of prophylactic antibiotics in women with a second-degree obstetric tear reduces the risk of infection and/or wound dehiscence by 50%, it will reduce the number of women with infections and/or wound dehiscence with 1500 annually in Denmark. The Number Needed to Treat (NNT) would be 10 to avoid one woman with infection or wound dehiscence. Optimizing the maternity period is essential for the mother, the child, and family formation, and it is therefore crucial to find ways to reduce the number of unnecessary stress factors, such as infections and wound dehiscence.

It is well-known that vaginal delivery and obstetric tears can cause long-term consequences like urinary and anal incontinence, pelvic organ prolapse, and affected sexual life, symptoms that can affect quality of life severely. Some studies indicate that second-degree tear can cause dyspareunia [8], decreased sexual activity 12 months postpartum [9], and increased perineal pain postpartum [10] compared to women with no perineal tear. However, it is unknown whether women with impaired healing with wound dehiscence or infection have a further increased risk of long-term complications. The results from our study can answer this question and show if prophylactic antibiotics decreases the risk of long-term symptoms.

## Trial status

This study is approved on 2 February 2023 with the EU-CT number: 2022–501930-49–00. Recruitment began on 21 March 2023. ClinicalTrials.gov Identifier NCT05830162. We expect the recruitment to be completed spring 2024.

## Data Availability

The four authors of this paper will have access to the final dataset when the last patient have had her last visit and the unblinding can be done.

## Abbreviations

GCP-unit: Good Clinical Practice unit
GDPR: General Data Protection Regulation
IQR: Interquartile range
NNT: Number Needed to Treat
